#### Secondary outcomes

All secondary outcomes are assessed at baseline (V2) and after 12 weeks (V4), except post COVID-19 related symptoms. Symptoms are assessed using online questionnaires prior to study visits (V1, V2, V4) and a symptom diary that is completed on a weekly basis between the baseline and 12-week visit.

*Post COVID-19 symptoms* are assessed using self-reported surveys prior to the screening visit (V1), baseline visit (V2), and end of intervention (V4) [1, 3, 11]. Participants complete a symptom diary on a weekly basis including severity grading.

*Fatigue* is assessed using the 13-item Functional Assessment of Chronic Illness Therapy—Fatigue Scale (FACIT-Fatigue) [33]. A cut-off score of < 34 will be used for descriptive analysis, and norm values from a German population [34] will be used for comparisons. The scale is responsive to treatment, and triangulated MIDs have been established for various patient populations [35]. In a small study (*n* = 32) with people attending COVID-19 rehabilitation, the MID for the FACIT-Fatigue scale has been estimated between 2.7 and 3.6 points [36]. This estimate will be used for the interpretation of between-group differences in this study.

*Dyspnea* is assessed using the Chronic Respiratory Questionnaire (CRQ) dyspnea domain [37–39]. The CRQ dyspnea domain consists of five questions rated on a 7-point scale. The instrument is valid, reliable, and responsive, with a reported MID of 0.5 units [40], which will be used to interpret between-group differences.

*Cognitive function* is assessed by trained personnel using the German version of the Montreal Cognitive Assessment (MoCA) test. The MoCA test is commonly used to evaluate cognitive function in people with COVID-19 and PCC [41–44], with a cut-off score < 26 for impairment [42, 45]. The standard correction for years of education will be applied.

*Anxiety and depression* are assessed with the Hospital Anxiety and Depression Scale (HADS) [46–48]. The scale includes 14 questions with a 4-point Likert-type scale. It is a valid and reliable instrument with a triangulated MID of 1.5–1.7 units change [30, 49, 50]. A cut-off value of 7 or higher will be used to report the number of participants with depression and/or anxiety [51].

*Health-related quality of life* is assessed with the EuroQol Questionnaire (EQ-5D-5L) questionnaire [27, 28]. The questionnaire includes five dimensions scored on five levels of severity. The Dutch value set will be used to calculate EQ-5D-5L index scores.

*Functional exercise capacity* is assessed with the 30-s sit-to-stand (STS) test [52–54]. A familiarization test is done at the screening visit (V1). Heart rate, oxygen saturation, and ratings of perceived exertion and dyspnea are recorded before and after the exercise test. A between-group difference of ≥ 2 repetitions post-intervention will be considered clinically relevant [53].

*Physical activity* is measured with a triaxial accelerometer (ActiGraph wGT3X-BT, Pensacola, FL, USA) worn around the hip for 8 consecutive days before baseline (V2) and study end (V4). Data will be used for the analysis if at least 4 days (including a weekend day) of measurements with a minimum of 10 h wear time per day are recorded. Physical activity will be expressed as daily step count and time spent in different intensity domains using validated cut-offs [55–57].

*Biomarkers of endothelial health* include soluble thrombomodulin, von Willebrand Factor antigen, syndecan-1, and sVCAM-1 [58–61] and are measured using commercially available enzyme-linked immunosorbent (ELISA) or Luminex (bead-based immunoassay) assays following the manufacturers instruction.

*Biomarkers of inflammation* include C-reactive protein (CRP), interleukin-6 (IL-6), and leukocyte levels [60, 62]. Blood levels of CRP- and IL-6, as well as leucocyte numbers as part of the hemogram, will be determined for each participant.

*Biomarkers of coagulation and platelet function* include soluble CD40 ligand (sCD40L) and plasma soluble P-selectin (sP-selectin) [58, 63–66] and will be measured using commercially available ELISA or Luminex assays following the manufacturers instruction. In addition, D-dimers, international normalized ratio (INR), activated partial thromboplastin time (aPTT), and platelet concentration as part of the hemogram will be assessed.

*Biomarker of oxidative stress* will be the total antioxidant capacity (TAC) of blood plasma using the fluorescence recovery after photobleaching (FRAP) method.

*Biomarkers of kidney and liver function* include serum creatinine levels to assess estimated glomerular filtration rate (eGFR), aspartate aminotransferase (ASAT), alanine aminotransferase (ALAT), and gamma-glutamyltransferase (γ-GT).

### Safety outcomes

At each study visit (Table 1), vital signs (heart rate, oxygen saturation, blood pressure, body temperature) are measured. Blood pressure is measured in duplicate after resting for 5 min in sitting position (legs uncrossed) with a portable blood pressure monitor (Omron M3 Comfort). The average blood pressure value will be recorded and used for the descriptive analysis. Heart rate and oxygen saturation are measured in sitting position with a portable pulse oximeter (Beurer PO 80).

At the screening visit (V1), a 12-channel resting ECG (ELI™ 280, Hechingen, Germany) is performed with the participant in supine position (after at least 5 min rest) to screen for unstable cardiac disease. Furthermore, a blood sample is drawn to screen for other underlying causes for symptoms similar as those seen in individuals with PCC. The tests include blood count, ferritin, CRP, vitamin B12 levels, and thyroid-stimulating hormone (TSH) as well as kidney function (eGFR) and liver enzyme activity (ALAT, ASAT, γ-GT). Clinically relevant abnormal diagnostic laboratory parameters will be passed on to the participants so that necessary measures can be taken such as further diagnostics or treatment delivered through the participant’s attending physician.

### Other outcomes

*Adherence to the study products* is evaluated during the follow-up visits (V3 and V4) and the two follow-up phone calls (P1 and P2) using a standardized assessment form. During the first follow-up visit (V3), the number of capsules returned by the participant is counted and recorded in the database. New capsules are handed out to study participants. During the second follow-up visit (V4), the remaining capsules returned by the participants are counted and recorded in the database.

### Evaluation of perceived study burden and study organization

Post-exertional malaise is a frequent symptom in PCC, and we are aware that the study visits may pose a burden on the participants. At each visit, starting with the baseline visit, participants are asked whether they experienced a worsening of their symptoms within 3 days after the last study visit. Upon completion of the study, participants receive an invitation to an online survey to provide feedback regarding the overall study organization (e.g., duration of visits, breaks, number of assessments). These assessments aim to gather insights from participants on how to improve the design and organization of future trials for both this vulnerable patient population and others.

### Spirometry

In addition, spirometry is performed according to the standards of the American Thoracic Society and European Respiratory Society [67] using portable spirometry (PADSY Spiro, Spirosound, Medset Medizintechnik GmbH, Hamburg, Germany). Forced vital capacity (FVC) and forced expiratory volume in 1 s (FEV_1_) are measured to screen for pulmonary obstruction (FEV_1_/FVC ratio below the lower limit of normal). *Z*-scores are calculated based on reference equations published by Quanjer et al. [68]. Spirometry data are used to characterize the patient cohort.

### Participant timeline {13}

A participant timeline including study visits and assessments is provided in Fig. 1. Study visits take place at the University of Zurich. In addition, we offer home visits for people who are unable to visit the study center due to their health condition. The study team considers a home visit when the distance from our institute to the patient’s home is no longer than 90 min (one way).

### Sample size {14}

Sample size calculations were based on data from a population-based prospective cohort study (Zurich SARS-CoV-2 Cohort) [3]. In this cohort (*n* = 1543), 208 (13.5%) study participants reported at least one symptom 6 months after the polymerase chain reaction (PCR) diagnosed SARS-CoV-2 infection [3]. The mean (SD) health status assessed with the EQ-VAS was 73.4 ± 16.5 on a 0–100 scale. Using the mean ± SD EQ-VAS data from this cohort and considering the MID of the EQ-VAS of 8 units [31] as reference, with 80% power, the estimated sample size is 136 subjects (i.e., 68 per group). This sample size allows us to detect a difference of 8 units in the EQ-VAS between the verum and placebo groups at 12 weeks. Assuming a drop-out rate of 10%, we aim to include a total of 150 subjects.

### Recruitment {15}

We are using various recruitment channels such as the ALTEA network (https://altea-network.com/en), the Long COVID Citizen Science Board [69], and the Long COVID Network Switzerland (https://long-covid-info.ch/). In addition, we share online flyers including information about the purpose of the study, the target group, and contact details of the study team with different stakeholders.

## Assignment of interventions: allocation

### Sequence generation {16a}

We used six different groups (A, B, C, D, E, F) with three representing placebo and three representing Pycnogenol®, where the allocation was unknown to the study team (see below). A senior biostatistician, not involved in the trial, generated a list of random numbers (block sizes of six representing the six different groups) using the package *blockrand* with the software R [70]. Note that we did not use varying block sizes because the probability that the study team could guess the allocation sequence is very low and because a block size of 12 seemed to be too large. Randomization is stratified for duration of PCC-related symptoms (≤ 6 months versus > 6 months) and presence of symptomatic chronic disease(s).

### Concealment mechanism {16b}

Computer-based randomization is done within the REDCap (Research Electronic Data Capture, Vanderbilt University, USA) database [71]. Study personnel performing randomization are unable to foresee the randomization sequence in REDCap due to restriction of user rights (i.e., no access to randomization module). At the end of the baseline visit (V2), following evaluation of inclusion and exclusion criteria, study participants are randomly assigned in a 1:1 ratio to receive Pycnogenol® or placebo.

### Implementation {16c}

A senior biostatistician, not involved in the trial, generated a list of random numbers. Upon evaluation of inclusion and exclusion criteria, trained study staff allocates participants to either the Pycnogenol® or placebo group in REDCap. The database provides a code (A, B, C, D, E, F), and study staff requests the appropriate study products according to pre-defined product labels. Each of the codes represents either Pycnogenol® or placebo and remains unknown to the entire study team until the study is completed. A team from our institute, not involved in the trial, was responsible for product labeling.

## Assignment of interventions: blinding

### Who will be blinded {17a}

Trial participants, team of investigators, outcome assessors, and data analysts are blinded to minimize information and measurement bias. Investigational products are identical in appearance and appropriately labeled, and the de-identification code is only accessible to the principal investigator.

### Procedure for unblinding if needed {17b}

In the event of a medical emergency or a suspected unexpected serious adverse reaction (SUSAR), unblinding is permissible. The unblinding process of the sponsor for the respected trial participant will take place at the latest possible time before the SUSAR reporting. If unblinding is needed, the principal investigator contacts the product labeling team to initiate the unblinding procedure for the respective participant. Unblinding will be recorded in the participants electronic case report form (eCRF).

## Data collection and management

### Plans for assessment and collection of outcomes {18a}

Study personnel underwent comprehensive training of all study processes including outcome assessments and database entries. Standard operating procedures (SOPs) are available for all study-specific assessments and processes. Database entries are monitored by an internal designated team member and an external monitor. Data from study visits are collected on case report forms (CRF) and are entered directly into the database after each visit. Questionnaires, most of which are validated instruments, are completed online by study participants, or on paper, if needed. Questionnaire data are inspected before each study visit. Missing data are added, and implausible entries are verified together with the participant.

Results from standard laboratory tests (ANALYTICA Medizinische Laboratorien AG, Zurich, Switzerland) are transmitted electronically via secured e-mail and entered into eCRFs. Data from biological samples, analyzed by our internal laboratory, are entered into eCRFs by trained study personnel. At the baseline visit (V2), participants are provided with a symptom diary, which they are required to return at their final study visit (V4). The symptom diary is discussed with participants during study visits and telephone calls to minimize missing data. Study personnel enters information from the diary into the eCRFs.

### Plans to promote participant retention and complete follow-up {18b}

To promote participant retention and complete follow-up data, we planned a short study visit 6 weeks after randomization and two phone calls to stay in close contact with study participants to build trust and confidence. If a participant chooses to discontinue their involvement in the study, we follow the following 3-step process: (1) we encourage the participant to complete the follow-up assessments according to the study protocol; (2) if the participant is unwilling to complete the assessments as outlined in the protocol, we inquire if they would be willing to complete the study assessments at the time of discontinuation; (3) in the event that the participant declines to complete a study visit, we encourage them to complete the assessment for the primary endpoint as per the protocol. Finally, we offer home visits for those who are not able to attend the study center. This enables individuals with severe PCC to participate in the study, thereby enhancing the likelihood of higher retention rates in the trial.

### Data management {19}

Data is collected using REDCap [71], a secure web-based application for managing research studies hosted at the Epidemiology, Biostatistics and Prevention Institute (EBPI) at the University of Zurich, Switzerland. A unique identifier is automatically generated within REDCap and is used for each participant on all study documents. All data are stored on a password-protected server and regular backups and software updates are performed. Team members have password-protected accounts with different levels of user access rights based on their roles in the study. Access to the database requests two-factor authentication.

Study participants complete online surveys upon e-mail invitation. Range checks are implemented in the database including online surveys to minimize data entry errors.

Our internal data quality manager checks database entries for correctness and plausibility. An external data monitor (MEDICRO GmbH, Petersaurach, Germany) ensures that the conduct, documentation, and reporting are in accordance with the study protocol, defined SOPs, Good Clinical Practice (GCP), and legal regulations. This includes correct issuance of investigational products as per randomization in REDCap and evaluation of the completeness of primary outcome information as well as completeness and correctness of adverse event reporting for all participants. Additionally, inclusion/exclusion criteria are checked for 50% of randomly selected participants. The data monitor is tasked with conducting various monitoring visits using a mix of on-site and off-site monitoring activities, including written reporting. The following visits and responsibilities are covered and carried out: pre-study visit, study initiation visit, routine monitoring visits, and close-out visit.

Key data to be monitored as per contract:100% source data verification for the first 5 study participants100% source data verification for an additional 30 randomly selected subjects (20% of *N* total)100% completion of case report forms including subject existence (no medical records)100% investigational medicinal product (IMP) dispensation100% primary endpoint assessment (EQ-VAS)50% inclusion/exclusion criteria verification for randomly selected participants100% adverse events (AE)/SAE reportingWritten reporting and review

Upon database closure, all data will be stored on servers of the University of Zurich, accessible to REDCap administrators. Access to study data and files is restricted to authorized study personnel. Coded data will be stored for 10 years. Paper documents that are generated in the context of the study are stored in a locked study closet. Prior to data analysis, data exports will be checked for outliers or implausible values.

### Confidentiality {27}

Confidentiality is ensured by utilizing participant identification codes to correspond to medical information and treatment data in the computer files. Each study participant receives a unique identifier that is automatically generated within the REDCap database. This code will be used for all study documents, labeling of blood tubes, and investigational products. The information linking the identifying personal data with the unique participant code is stored separately on a password-protected participant identification list on a secure server of the University of Zurich. After finalization of data collection, the password of the participant identification list will be changed so that the file will remain accessible only to the sponsor and principal investigator (PI).

### Plans for collection, laboratory evaluation and storage of biological specimens for genetic or molecular analysis in this trial/future use {33}

Standard clinical parameters are analyzed externally by a certified diagnostic laboratory (ANALYTICA Medizinische Laboratorien AG, Zurich, Switzerland). Study-specific analyses of blood biomarkers are done in our in-house laboratory. Plasma samples for the in-house analyses are aliquoted and stored frozen until sufficient number of samples are acquired for batch analysis.

If consent for further use of data and biological material in coded form has been given, surplus samples after completion of the PYCNOVID study will be transferred to our biobank, where they will be preserved for potential future research use. In case that the biological material is no longer needed or consent for further use has not been given or is withdrawn with the request to destroy the remaining samples, it will be destroyed in compliance with the University of Zurich standards for biological waste disposal and will be documented in a project-specific laboratory journal.

## Statistical methods

### Statistical methods for primary and secondary outcomes {20a}

#### Primary outcome

The primary analysis will be done following the intention-to-treat (ITT) principle. All randomized participants having received at least one dose of Pycnogenol® will be included in this analysis. We will use multivariable linear regression models to compare EQ-VAS values at 12 weeks adjusted for baseline values and stratification factors, i.e., PCC duration (≤ 6 months versus > 6 months) and presence of any chronic disease(s).

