### Trial design {8}

This is a 12-week, single-center, placebo-controlled, quadruple-blind, parallel design superiority trial investigating effects of a daily dose of 200 mg Pycnogenol® versus a placebo. Randomization (1:1 allocation ratio) will be stratified for duration of PCC-related symptoms (i.e., ≤ 6 months vs. > 6 months) and presence of symptomatic chronic conditions.

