## Interventions

### Explanation for the choice of comparators {6b}

We choose a patient-reported outcome as primary endpoint in this study (EQ-VAS) [27, 28]. To differentiate the potential effects of Pycnogenol® from the placebo effect, this study utilizes a placebo that shares identical physical characteristics and dosing regimen with the verum. Using a placebo is ethically justified, as there is no approved treatment for PCC, and no treatment of proved effectiveness will be withheld. Additionally, participants are not required to discontinue any PCC-related treatment or medication prior to enrolment into the study, except regular intake of Pycnogenol®.

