**Table 1 Tab1:**
[figure not shown]
Overview of enrolment, assessments and outcome measures according to Standard Protocol Items: Recommendations for Interventional Trials (SPIRIT)

*Abbreviations*: *CRQ*, Chronic Respiratory Questionnaire; *EQ-5D-5L*, EuroQol Questionnaire (5 levels); *EQ-VAS*, EuroQol Visual Analogue Scale; *FACIT-Fatigue*, Functional Assessment of Chronic Illness Therapy—Fatigue Scale; *HADS*, Hospital, Anxiety and Depression Scale; *MoCA*, Montreal Cognitive Assessment Test

^*^Primary outcome: The EQ-Visual Analogue Scale is assessed daily over 7 consecutive days prior to the baseline visit (V2) and follow-up visit 2 (V4)

^**^Blood biomarkers of inflammation, coagulation and platelet function, oxidative stress, and endothelial function

^***^Study visits can potentially impose a burden on participants. At each visit, starting with the baseline visit (V2), participants are asked whether they experienced a worsening of their PCC-related symptoms within 3 days after the last study visit

^****^Upon completion of the study, participants receive a link to an online survey to request feedback regarding the study organization

Participants in the intervention group receive 200 mg Pycnogenol® per day for 12 weeks, with two capsules containing each 50 mg in the morning and two capsules in the evening. Pycnogenol® is a proprietary French maritime pine bark extract (Pinus pinaster subsp., atlantica, Pinaceae) produced by Horphag Research, Geneva, Switzerland. Pycnogenol® is standardized to contain 70 ± 5% procyanidins in compliance with the United States Pharmacopeia. Its compounds and gut metabolites are known among other actions for their antioxidant properties, anti-inflammatory activities, and stimulation of nitric oxide production in vascular endothelial cells [22].

Participants in the control group receive a placebo. The placebo capsules are manufactured in the same facility and have the same physical appearance, consistency, and weight as the verum. Like the participants in the verum group, participants in the control group take two capsules twice daily with or right after a meal.

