### Strategies to improve adherence to interventions {11c}

To enhance the validity of our data and adherence to study products, we planned a short study visit six weeks and two phone calls two respectively 9 weeks after randomization (Fig. 1) to stay in close contact with study participants. During the phone calls, the importance of adhering to the study products and monitoring symptoms in the diary is discussed. Study products returned at the follow-up visits (V3, V4, Fig. 1) are counted and recorded in the database. In addition to the intention-to-treat analysis (primary analysis), we plan a per protocol analysis based on adherence to study products and investigate its potential impact on primary and secondary outcomes.

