#### Primary outcome

The primary outcome is self-reported health status assessed with the EQ-VAS, also known as the “Feeling Thermometer” [27, 28]. The EQ-VAS is numbered from 0 to 100 with 0 representing the “worst imaginable health” and 100 representing the “best imaginable health.” The scale is frequently used in people with chronic respiratory conditions [30–32] and has a well-established minimal important difference (MID) of 5–8 units [31]. In our trial, EQ-VAS is assessed daily over seven consecutive days prior to the baseline visit (V2) and again prior to the last study visit (V4). Mean EQ-VAS scores (i.e., pre- and post-intervention) will be computed, including at least 4 days. Post-intervention, EQ-VAS scores will be compared between the intervention and placebo groups and adjusted for baseline values. In addition, self-reported health status is assessed at screening (V1) visit. These data will be used for descriptive purposes. A minimal important difference (MID) of 8 units will be used for interpretation of the magnitude and clinical relevance of between-group differences in post-intervention EQ-VAS values [31].

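### The primary analysis is labelled intention-to-treat, but its stated set requires a dose of Pycnogenol: literally no placebo participant qualifies, and read as study product it is modified ITT

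*Protocol article*

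**What the plan says.** The Primary outcome paragraph under Statistical methods {20a} opens with the principle: "The primary analysis will be done following the intention-to-treat (ITT) principle". The next sentence sets the membership rule: "All randomized participants having received at least one dose of Pycnogenol® will be included in this analysis". The paragraph then specifies a linear regression comparing EQ-VAS at 12 weeks, adjusted for baseline and the stratification factors.

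Section {11c} repeats the label without any dose condition: "In addition to the intention-to-treat analysis (primary analysis), we plan a per protocol analysis based on adherence to study products". The intervention description, in the text that follows Table 1, states what the other arm gets: "Participants in the control group receive a placebo". The Primary outcome paragraph under Outcomes {12} states the contrast: "EQ-VAS scores will be compared between the intervention and placebo groups and adjusted for baseline values".

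No section of the article gives a different definition of the primary set, or extends the dose condition to placebo or to study product in general.

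**The concern.** Two adjacent sentences disagree about who is in the primary analysis. The first promises the randomised groups. The second makes entry depend on having had the active product, which one of the two groups never gets from the trial.

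At stake is the set behind the trial's only primary comparison. The text as it stands allows at least three different sets: Pycnogenol participants only; a dose condition on the Pycnogenol arm with the placebo arm taken whole; or at least one dose of either product. None of these is all randomised participants as allocated. If the sentence is left alone, the choice between them could be made after the data are seen, and any of them could still be reported as ITT.

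**Working it through.** **1. The plan's own figures.** The disputed sentence contains no number, so the sample size serves only to show the scale. Inputs from Sample size {14}: difference 8 units, SD 16.5, power 80%, 68 per group (136), raised to 150. Alpha is not stated; two-sided 0.05 is assumed.

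- Normal approximation: n = 2 × (1.960 + 0.842)² × 16.5² / 8² = 66.8, so 67 per arm.
- Two-sample t-test: 67.75, so 68 per arm, which matches the plan.

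The point does not rest on an error in these figures.

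**2. The literal set.** Allocation: "Randomization (1:1 allocation ratio) will be stratified for duration of PCC-related symptoms". So 150 / 2 = 75 participants per arm. Control participants get placebo capsules. Regular Pycnogenol users are excluded, and the comparator section confirms that this is the one treatment a participant may not bring into the trial ("except regular intake of Pycnogenol"). Participants qualifying through trial product: up to 75 in the Pycnogenol arm and 0 of about 75 in the placebo arm. With an empty comparator, no between-group difference can be estimated, although Objectives {7}, Outcomes {12} and the regression in {20a} all require one.

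**3. The study-product reading.** Timing of allocation: "At the end of the baseline visit (V2), following evaluation of inclusion and exclusion criteria, study participants are randomly assigned in a 1:1 ratio". Product is requested only after the allocation code is issued (Implementation {16c}). Any dose therefore comes after randomisation, and requiring one is a post-randomisation condition. That makes the set modified ITT. It is a common choice, but not what {20a} and {11c} name.

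**4. Size under the study-product reading.** The number never dosed is not in the article, so k per arm is assumed. Power ≈ Φ(8 / (16.5 × √(2/n)) − 1.960) with n = 75 − k, unadjusted for baseline and with outcomes available for all those included:

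| k per arm (assumed) | n per arm | Power |
|---|---|---|
| 0 | 75 | 84.4% |
| 2 | 73 | 83.4% |
| 5 | 70 | 81.8% |
| 8 | 67 | 80.1% |

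For k = 0: 8 / (16.5 × 0.1633) = 2.969; 2.969 − 1.960 = 1.009; Φ = 0.844.

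**5. Size if the condition fell on the Pycnogenol arm only.** The article does not state this rule, so this is illustration only. If m of 75 are never dosed and their outcome is D units below that of the others, leaving them out raises the arm mean by (m/75) × D. With assumed m = 2 and D = 5: 2/75 × 5 = 0.13 units. With assumed m = 7 and D = 16.5: 7/75 × 16.5 = 1.54 units. The planned difference is 8.

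**The case against.** The strongest reply is that the literal reading is a drafting slip. The same paragraph goes on to describe a between-group regression, the trial is defined throughout as Pycnogenol against placebo, and the article uses the neutral term study products elsewhere. No analyst could carry out the literal rule. This stands: the literal reading shows that the sentence is wrong, not that the trial will be analysed without a control arm. The slip still leaves the ITT contradiction, because substituting study product does not remove the dose condition. Section {11c}, which names ITT with no such condition, supports the slip explanation but does not correct the rule in {20a}.

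Three stronger conclusions might be inferred, and the documents do not support them.

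- A reader might take the 10% drop-out allowance (0.10 × 150 = 15) as the number whose inclusion is in doubt. That allowance is not a count of people never dosed. Someone who takes one dose and then leaves stays in the set, with missing final-visit data imputed under {20c}.
- A reader might infer that early leavers could not be classified as dosed or not. Section {11b} offers a termination visit or a phone call and asks for leftover product, and adherence is also recorded at V3, V4 and both calls. Product dispensing is monitored for all participants, so if received means dispensed, membership is documented. Only someone who refuses all contact might remain uncertain on intake.
- A reader might infer that a dose condition undoes randomisation. Participants and staff are blinded and the capsules look alike, so whether a first capsule is taken cannot readily depend on allocation. Applied equally to both arms, the condition usually causes little bias.

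**Conclusion.** The primary set is wrong as written. Literally it contains 0 of about 75 placebo participants and cannot deliver the specified comparison. In its most plausible intended meaning, at least one dose of either product, it is a modified ITT set under an ITT label. This is a stated rule that contradicts its own heading, not a detail left to an unseen analysis plan.

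The practical effect under that meaning is probably small. This rests on few participants never being dosed, a number the article does not give, and on blinding holding. The power figures also assume two-sided alpha 0.05 and SD 16.5. They show that losing a few never-dosed participants costs little power, and equally that power gives no reason to exclude them. The case for correction is that the set must be unambiguous and correctly named before allocation is known; no material bias has been shown.

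**What to change.** Replace the membership sentence in {20a} with: *All randomised participants are analysed in the arm to which they were randomised, regardless of whether or how much study product they took.* Add that missing V4 data are handled by the multiple imputation already planned in {20c}. The rest of the article supports this: section {18b} already seeks the primary endpoint from participants who discontinue.

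If a dosed set is also kept, define it as at least one dose of study product (Pycnogenol or placebo), label it modified ITT, and report the number excluded in each arm. Carry the same wording into the analysis plan.

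The cost is one sentence, changed before unblinding. No new data or extra participants are needed.
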